### Statistical analysis

SPSS version 17.0 or higher will be used for statistical analysis. Descriptive statistics will be used to describe demographic data and baseline characteristics and follow-ups for each treatment group. Two-way mixed ANOVA will be used to determine within-subject and between subject variables. Main effects for independent variables (local treatment/sensorimotor exercise and local treatment/balance exercise) and the intervention effects of the independent variables immediately after treatment and at 3, 6 and 12 month follow-ups will be analyzed. This allows the individual effects of sensorimotor exercise and balance exercise to be examined as well as whether there will be an additive effect of applying both sensorimotor and balance exercises in a multimodal treatment. Differences in mean change (baseline minus follow-up) will be compared between groups using baseline values of the outcomes as covariates.

Effect sizes will be calculated by taking the difference in mean changes in the primary outcomes between the intervention groups and control group (local neck treatment alone). An effect size of 0.2 will be regarded as small, 0.5 as medium and 0.8 as large [55]. Main comparative analysis for primary and secondary outcomes will be performed using an intention-to-treat approach. To address missing data, multiple imputation will be performed as a sensitivity analysis. The significance level will be set at 0.05.

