## Methods/design

### Trial design

The trial utilizes a single blind 2 × 2 factorial design, and conforms to the CONSORT recommendations [33].

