### Procedure

Eligible participants who have agreed to participate in the study will be randomly allocated to one of four treatment groups; local neck treatment (cervical mobilization and therapeutic exercise), local neck treatment combined with sensorimotor control exercises, local neck treatment combined with balance exercises, or local neck treatment combined with sensorimotor control and balance exercises. Interventions will be provided in 12 physiotherapy sessions over a 6-week intervention period (2 visits per week) [26]. Baseline and follow-up assessments (post-treatment and 3, 6 and 12 months) will be conducted at the Department of Physical Therapy, Chiang Mai University by an assessor who is blinded to treatment allocation. The participants will be requested to refrain from seeking other forms of treatment during the trial. Medication for pain may be taken, if necessary, but the participants will be asked to record the type and dose of medication in a medication diary. The flow chart of the trial is presented in Fig. 1.

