### Randomization and allocation concealment

All eligible participants will be randomly allocated to one of four intervention groups: i) local neck treatment, ii) local treatment plus sensorimotor control exercises, iii) local treatment plus balance exercises, or iv) local treatment plus sensorimotor control and balance exercises. Randomization will be undertaken by an independent person with no other involvement in the trial. Random sequence will be generated by a computer permuted blocks of eight, stratified by age (≤ or > 45 years old) and dizziness (yes or no), with allocation ratio 1:1:1:1. Allocation will be concealed in sequentially numbered, sealed, opaque envelopes.

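### The named two-way mixed ANOVA does not fit a 2 × 2 factorial with repeated visits, and the plan does not say which of its two analyses is primary

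*Protocol article*

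**What the plan says.** The Trial design section states: "The trial utilizes a single blind 2 × 2 factorial design". The four arms are (i) local neck treatment, (ii) local plus sensorimotor, (iii) local plus balance and (iv) local plus both, "with allocation ratio 1:1:1:1". The Procedure section gives five assessments: "Baseline and follow-up assessments (post-treatment and 3, 6 and 12 months").

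The Statistical analysis section then makes three statements that bear on the main model.

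- The model: "Two-way mixed ANOVA will be used to determine within-subject and between subject variables".
- The targets: "Main effects for independent variables (local treatment/sensorimotor exercise and local treatment/balance exercise"), with intervention effects at each follow-up, and "whether there will be an additive effect of applying both sensorimotor and balance exercises in a multimodal treatment".
- A further comparison: "Differences in mean change (baseline minus follow-up) will be compared between groups using baseline values of the outcomes as covariates".

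A later paragraph of the same section adds effect sizes for each intervention group against local treatment alone. The section does not say whether the between-subject part is one four-level group or two two-level factors. It does not name a sensorimotor × balance term, and it does not rank the mixed ANOVA against the baseline-adjusted comparison.

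**The concern.** The Background asks whether one, both or neither form of training is needed on top of conventional treatment. In a 2 × 2 factorial that question is answered by three single-df quantities: the effect of sensorimotor exercise, the effect of balance exercise, and their interaction. The model label points to group × time, whose standard output is an omnibus test across four groups and an omnibus group-by-time test. A significant omnibus result says only that the arms differ somewhere.

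The baseline-adjusted change comparison is a different test of the same treatment effects. With neither designated as primary, the choice could be made after both results are known.

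**Working it through.** **Counting factors.** Two-way mixed, read conventionally: 1 between-subject + 1 within-subject = 2 factors. This design: sensorimotor + balance + visit = 3 factors. The label is one factor short.

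**What each form tests over the four follow-ups** (4 arms × 4 visits = 16 means, so 15 model df):

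| Form | Terms and df |
|---|---|
| Group × visit | group 3, visit 3, group × visit 9; total 15 |
| Sensorimotor × balance × visit | S 1, B 1, S×B 1, visit 3, S×visit 3, B×visit 3, S×B×visit 3; total 15 |

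The second row splits the 3 and the 9 of the first into named parts. In terms of arm means:

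- sensorimotor effect = (ii + iv)/2 − (i + iii)/2
- balance effect = (iii + iv)/2 − (i + ii)/2
- interaction = (iv − iii) − (ii − i)

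**Check that the two forms are the same model.** Both were fitted to simulated data with 35 per arm (the plan's number before dropout) and 4 visits.

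- Model df: 15 and 15. Residual sum of squares: 969.76 and 969.76. Largest difference in fitted values: about 1e-14.
- Group sum of squares on 3 df: 4.749 = 0.032 (S) + 1.979 (B) + 2.738 (S×B).
- Group × visit sum of squares: 8.335 = 1.989 + 2.592 + 3.754.

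So a four-level group model contains every factorial effect. It does not display them unless the contrasts are requested.

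**Would relying on the omnibus test cost power?** Take 35 per arm, N = 140, 136 denominator df, one active factor with standardised effect d, and noncentrality λ = 35d².

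| d | Source | λ | Power, 1 df | Power, 3 df |
|---|---|---|---|---|
| 0.4775 | chosen to give 80% | 7.98 | 80.1% | 63.9% |
| 4.5/3.2 = 1.41 | Sample size section, JPE | 69.2 | >99.9% | >99.9% |
| 21.9/12.3 = 1.78 | Sample size section, sway | 111.0 | >99.9% | >99.9% |

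The loss appears only at an effect that the protocol does not state.

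**Would coding baseline as a level of time matter?** Assume compound symmetry with visit correlation r and a constant effect after treatment. The group main effect averaged over five visits is then 4/5 = 0.8 of the true effect, with variance proportional to (1 + 4r)/5. The baseline-adjusted mean of four follow-ups keeps the full effect, with variance proportional to (1 + 3r)/4 − r².

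Relative efficiency = [0.8² / ((1 + 4r)/5)] × [(1 + 3r)/4 − r²] = 0.56, 0.40, 0.24 at r = 0.3, 0.5, 0.7.

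Power where the baseline-adjusted test has 80% = Φ(2.80√ratio − 1.96) = about 55%, 43%, 28%.

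The arithmetic is sound, but the protocol does not say that baseline is a level of time.

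**Precision of the interaction.** In SD units at a single visit, unadjusted, with 35 per arm:

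- SE of a main effect = √(2/70) = 0.169
- SE of the interaction = √(4/35) = 0.338, twice as large

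Multiplying by 1.96 + 0.84 = 2.80, the effects detectable with 80% power are about 0.47 SD and 0.95 SD.

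**The case against.** The strongest reply is that the paragraph must be read as a whole. The sentences after the model name set the two exercise effects and their combination as the targets: "This allows the individual effects of sensorimotor exercise and balance exercise to be examined as well as whether there will be an additive effect". On that reading, two-way refers to the two exercise factors and mixed adds visit. The Sample size section, which lists two-way ANOVA and repeated-measures ANOVA as separate elements, gives this some support. The labels that pair local treatment with each exercise can likewise be read as without versus with the add-on. A list of model terms and the contrast coding may also sit in an analysis plan that is not shown.

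Much of this stands. A reader might infer that the named model cannot yield the separate and additive effects. That is not so: the two forms are the same model, and the effects are declared as targets. A reader might also infer that the trial will lose power, from 80% to 64% or lower. The documents do not support that either. The first figure uses an effect chosen to give 80% power, far below the stated 1.41 and 1.78 SD. The lower figures require baseline to be a level of time, whereas the text lists effects at the follow-ups and uses baseline as a covariate in its change comparison. Even with baseline in the time factor, treatment effects would ordinarily be read from group × time.

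The reply does not repair the label, which in ordinary usage describes another design. The interaction still has to be guessed from the wording about additivity. The order of the two analyses is also unstated. These are defects in what the article does state, not details left to a fuller document.

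**Conclusion.** The point holds as a misnamed and incompletely specified primary model, together with two analyses of the same effects of which neither is designated primary. It bears on the primary objective, because the default tests of the model as named do not isolate the three effects that answer it. It does not show that the analysis is incapable of answering the question, and it puts no number on this trial's power; the power figures under the check are illustrations only.

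The conclusion rests on the conventional meaning of two-way mixed ANOVA and on the section's silence about ranking. It is a moderate point that wording can settle, and it is best settled before analysis, since the protocol reports that recruitment has begun.

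**What to change.** Replace the two-way mixed ANOVA with one primary model for each primary outcome measure. Use the four follow-up values as the response, with sensorimotor (yes/no) × balance (yes/no) × visit and the baseline value of the outcome as covariate. Group × visit with the same covariate and the three factorial contrasts prespecified is equivalent. This stays close to the plan's own baseline-adjusted comparison: with baseline as covariate, analysing change or follow-up value gives the same treatment estimate apart from sign.

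Report, with 95% confidence intervals:

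- the sensorimotor effect, arms ii + iv versus i + iii;
- the balance effect, arms iii + iv versus i + ii;
- their interaction;
- always beside these, the simple effects of arms ii, iii and iv against local treatment alone.

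Showing the simple effects in every case avoids a rule that depends on how large the interaction turns out to be. State that any other analysis is supportive.

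The cost is analysis-plan wording, with the same data and software. The drawback is that the interaction will be imprecise (standard error twice that of a main effect) and should be described so; a non-significant interaction should not be reported as proof of additivity.

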### Outcome measures (Table 5)

#### Primary outcomes

##### Postural stability

A sway meter will be used to measure the extent of postural sway and displacement. The sway meter is a simple tool for assessing postural sway in individuals with impaired balance [38]. It has been shown to have good test-retest reliability (ICCs = 0.65-0.94) and good validity (r with forceplate = 0.56-0.87) [38]. The sway meter consists of a 40 cm long rod with a vertically mounted pen at its end. It will be firmly attached to the participant’s waist using a webbing strap. During the test, the pen will record participant’s sway on a millimeter graph paper fastened to the top of an adjustable-height table. Maximum displacement in anterior-posterior (APmax) and medial-lateral (MLmax) directions and total sway (number of square millimeter squares traversed by the pen) will be recorded. The postural sway will be measured in 8 conditions as follows: narrow stance (feet close together) on firm and soft surfaces with eyes open and eyes closed [39] and during a neck torsion maneuver (head turned 45° to the left and right) on firm and soft surfaces [40]. Participants will be tested barefoot and asked to stand still without talking for 30s for each condition. Participants are allowed a maximum of two additional attempts if they are unable to maintain the position for 30s. A rest period of 60s will be given between each condition.

**Table 5 Tab5:** Summary of outcome measures

Primary outcome measures	Data collection instruments
Postural stability	A swaymeter
- Sway displacement	
- Sway area	
Cervical joint position error	A laser-pointer attached to a lightweight headband
Secondary outcome measures	
Gait speed	10-m walk test
Dizziness intensity	VAS (0-100 mm)
Neck pain intensity	VAS (0-100 mm)
Neck disability	NDI-TH (0-100)
Pain extent and location	iPad and custom software
Cervical range of motion	A CROM instrument
Functional ability status	PFSF (scale range 0-10)
Health-related quality of life	Thai SF-36 (scale range 0-100)
Global perceived benefit of treatment	A seven-point ordinal Likert scale (1-7)

All outcome measures will be recorded at baseline, immediately after intervention, 3, 6 and 12 months follow-ups. *VAS* Visual analogue scale, *NDI-TH* Neck disability index-Thai version, *Thai SF-36* Thai version of short form 36, *CROM* Cervical range of motion, *PFSF* The patient-specific functional scale

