### Sample size

The sample size estimates are calculated based on the primary outcomes (postural stability and cervical JPE) from baseline to follow-ups. According to our previous data, we consider a sample size that gives 80% power with a 5% confidence level to detect a significant difference of 21.9 cm^2^ (SD = 12.3) for postural sway and 4.5° (SD = 3.2) for JPE. Sample size estimates were performed using both two-way ANOVA and repeated measure ANOVA (two-tailed) and the optimum number of 35 participants per group is required. To allow for 20% drop out rate, a total sample size of 168 participants (42 per group) will be recruited for this trial.

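### Two analyses of the primary outcomes treat baseline differently and neither is named as decisive; if the mixed ANOVA includes the baseline visit, its main effects understate the treatment effect

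*Protocol article*

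**What the plan says.** All points are from the protocol article.

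- Statistical analysis names the model: "Two-way mixed ANOVA will be used to determine within-subject and between subject variables". It then lists main effects of the two exercise factors, and adds that "the intervention effects of the independent variables immediately after treatment and at 3, 6 and 12 month follow-ups will be analyzed". The visits named there are all post-treatment. The levels of the within-subject factor are not listed.
- The same paragraph ends with a baseline-adjusted comparison: "Differences in mean change (baseline minus follow-up) will be compared between groups using baseline values of the outcomes as covariates".
- The next paragraph defines the effect size: "Effect sizes will be calculated by taking the difference in mean changes in the primary outcomes between the intervention groups and control group". It does not say whether this difference is adjusted for baseline.
- The word main is attached to an analysis set, not to a model: "Main comparative analysis for primary and secondary outcomes will be performed using an intention-to-treat approach".
- The footnote to Table 5 gives the visit schedule: "All outcome measures will be recorded at baseline, immediately after intervention, 3, 6 and 12 months follow-ups". That is one pre-treatment and four post-treatment visits.
- Sample size describes the time span thus: "The sample size estimates are calculated based on the primary outcomes (postural stability and cervical JPE) from baseline to follow-ups". It names both a two-way and a repeated-measures ANOVA as the method of calculation.

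**The concern.** The paragraph describes two ways of testing the same outcomes, and they use baseline differently. A mixed ANOVA on raw scores either takes baseline as one more visit or leaves it out. The change-score comparison takes it as a covariate. The tests can disagree on the same complete data, even with correct factorial coding, and no sentence says which one answers the primary hypothesis. The choice could therefore be made after the results are seen.

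The size of the reported effect is also open. In a mixed ANOVA that contains baseline, the between-subject main effect is an average over all visits. One of these precedes treatment, and its expected between-arm difference under randomization is zero. Reported as the treatment effect, that average is too small.

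**Working it through.** **Inputs from the protocol article.** Five visits, one before and four after treatment. Planned differences 21.9 cm² (SD 12.3) for sway and 4.5° (SD 3.2) for joint position error. 35 per group after dropout, 42 per group recruited, 168 in total, 20% dropout.

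**Assumptions, because the article gives no figure.** Equal effect at all four follow-ups. Equal correlation r between any two visits, shown for 0.4, 0.6 and 0.8. For the power illustration, a true main effect of one exercise factor of 1° with SD 3.2, so δ = 1/3.2 = 0.3125 SD. Completers 168 × 0.8 ≈ 134, so 67 v 67 across each factor.

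**Step 1: size of the dilution if baseline is a time level.** Expected main effect = (0 + 4δ)/5 = 0.80δ. At the planned effects, 0.80 × 4.5 = 3.6° and 0.80 × 21.9 = 17.5 cm². Two other quantities from the same ANOVA are not diluted: the group-by-time contrast (follow-ups minus baseline) and the effect at each follow-up.

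**Step 2: variances of a participant's summary, in SD² units.**

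- Mean of four follow-ups, adjusted for baseline: (1 + 3r)/4 − r²
- Mean of five visits: (1 + 4r)/5, with effect 0.80δ
- Mean of four follow-ups, unadjusted: (1 + 3r)/4, with effect δ

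At r = 0.6 these are 0.70 − 0.36 = 0.34, 0.68 and 0.70. At r = 0.4 they are 0.39, 0.52 and 0.55. At r = 0.8 they are 0.21, 0.84 and 0.85.

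**Step 3: power.** SE = √(variance × 2/67); power ≈ Φ(effect/SE − 1.96). At r = 0.6:

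- Adjusted: SE 0.1007, 0.3125/0.1007 = 3.10, power 87%
- Five-visit main effect: SE 0.1425, 0.25/0.1425 = 1.75, power 42%
- Unadjusted follow-ups: SE 0.1446, 0.3125/0.1446 = 2.16, power 58%

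| r | Adjusted | Five-visit main effect | Unadjusted follow-ups |
|---|---|---|---|
| 0.4 | 83% | 52% | 68% |
| 0.6 | 87% | 42% | 58% |
| 0.8 | 98% | 35% | 50% |

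**Step 4: efficiency relative to the adjusted analysis.** For the five-visit main effect this is 0.64 × adjusted variance / five-visit variance: 0.64 × 0.39/0.52 = 0.48 at r = 0.4, 0.64 × 0.34/0.68 = 0.32 at r = 0.6, and 0.64 × 0.21/0.84 = 0.16 at r = 0.8. For unadjusted follow-ups it is 0.39/0.55 = 0.71, 0.34/0.70 = 0.49 and 0.21/0.85 = 0.25.

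**Step 5: the same check at the protocol's own effects.** 4.5/3.2 = 1.41 SD and 21.9/12.3 = 1.78 SD. With 35 per group, even the diluted five-visit main effect has power above 99.9% for r up to 0.8. For joint position error at r = 0.8: 0.80 × 1.406 = 1.125; SE = √(0.84 × 2/35) = 0.219; 1.125/0.219 = 5.1.

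**The case against.** The strongest reply is that the paragraph describes one analysis in three steps: the model family, then the effects of interest, then the response and covariate. The repeated measures would be four change scores, with baseline as covariate. Adjusting change for baseline gives the same treatment effect, apart from sign, as adjusting the follow-up score for baseline, so this would be essentially the right analysis and nothing would be diluted. The effect-size sentence follows directly and could be read as the adjusted difference. This reading is possible, but the text does not state it. The ANOVA and the covariate comparison stand as separate sentences, one in terms of factor main effects and the other in terms of groups.

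A reader might infer from the sample size wording that baseline is definitely a level of the time factor, and so that the planned main effect is diluted. The documents do not support that. The wording describes the basis of the sample size and fits change from baseline equally well, and the only visits listed for intervention effects come after treatment.

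A reader might also infer that the trial risks missing its planned effects. It does not: at those effects all the candidate tests would detect a difference. The wide power gaps appear only for smaller effects such as the assumed 1°. Such effects are plausible because every arm receives active local treatment, but the protocol does not plan for them.

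Finally, a condensed article may leave the exact model to a fuller document. That would excuse silence. Here the article does specify the analysis, and in a form that allows two tests with different answers.

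**Conclusion.** The point holds in a limited form. Two treatments of baseline are written for the primary outcomes and neither is made decisive. That much rests on the text alone.

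The consequence depends on an unstated detail. If baseline is a time level, the factor main effect is 20% too small under a constant post-treatment effect, while the group-by-time and per-visit contrasts are not affected. If raw follow-ups alone are analysed, the estimate is unbiased but less precise, with relative efficiency about 0.71 at r = 0.4 and lower at higher correlations. If the intended analysis is baseline-adjusted change, neither problem arises.

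The power figures are illustrations that rest on an assumed 1° effect, equal correlations and equal effects over follow-up. At the planned effects the issue is the size of the reported estimate and the freedom to choose between tests, not detection. It is worth correcting, but it does not undermine the design.

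**What to change.** For each primary outcome, name one deciding model: the four follow-up visits as responses, the two exercise factors and visit as explanatory terms, and the baseline value of the outcome as covariate only, not also as a level of the visit factor. State which visit or contrast from that model decides. Take the factorial effects, confidence intervals and effect sizes from the same model, so that the reported size and the test agree. Label any ANOVA main effect that includes the baseline visit as descriptive. The cost is wording only: the data, visits, sample size and software do not change.

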For those provisionally eligible for the trial, appointments will be made with an experienced physiotherapist who will be blinded to participant group allocation if accepted for the trial. The experienced physiotherapist will perform a physical examination of the neck and test sensorimotor function and balance. The physical examination includes:*Tests of cervical joint position error (JPE)* [9, 13]*.* The task is to return to the starting position as accurately as possible with the blindfold. Three trials will be performed of right and left rotation and extension. An average absolute error of > 4.5° in any direction is indicative of a deficit in cervical joint position sense [34].*Tandem stand test* [35]. The participants stand heel to toe with the dominant foot behind the non-dominant foot on a firm surface with eyes closed (age ≤ 45 years) or with eyes open (age > 45 years) [36]. An inability to maintain the standing position without taking a step for 30 s indicates balance impairment [36].*Manual examination of the cervical spine.* The physiotherapist will palpate the cervical facet joints from C0-1 to C7-T1 bilaterally. A joint will be classified as symptomatic by a combination of pain provoked > 2/10 and the physiotherapist’s rating of at least moderately abnormal tissue resistance [37].

All participants will be provided information about the study and enrolled into the trial if they meet all eligibility criteria and voluntarily sign an informed consent statement.

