##### Cervical JPE

Cervical JPE will be measured using a laser-pointer attached to a lightweight headband as described by Revel et al. [13]. Participants will be seated 90 cm away from the target. They will be blindfolded and asked to perform an active movement (extension and rotation to the left and right) and return to the starting head position as accurately as possible. An absolute error between the starting and end points will be calculated in millimeters and then converted to degrees. Three repetitions of each movement direction will be undertaken and the mean value of the error will be used for analysis. This method has been shown to have good test-retest reliability (ICCs = 0.73-0.84) and high validity (r with three-dimensional ultrasound based technique = 0.95) [41].

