### Blinding

The baseline and follow-up assessments will be performed by an independent assessor who is blinded to treatment allocation. The physiotherapists providing the intervention will not be blinded to treatment but will be blinded to outcome assessments throughout the trial.

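### Joint position error appears to be read twice before treatment, but the analysis adjusts for the baseline reading only, leaving a small amount of precision unused

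*Protocol article*

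**What the plan says.** **Screening.** Under Participants, the pre-enrolment visit is described thus: "The experienced physiotherapist will perform a physical examination of the neck and test sensorimotor function and balance". For JPE, "Three trials will be performed of right and left rotation and extension", blindfolded, and "An average absolute error of > 4.5° in any direction is indicative of a deficit in cervical joint position sense". People are then "enrolled into the trial if they meet all eligibility criteria and voluntarily sign an informed consent statement".

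**Baseline.** Under Procedure, which concerns people already eligible and agreed, "Baseline and follow-up assessments (post-treatment and 3, 6 and 12 months) will be conducted at the Department of Physical Therapy". Under Blinding, "The baseline and follow-up assessments will be performed by an independent assessor who is blinded to treatment allocation". Table 5 has every outcome recorded at baseline. The Cervical JPE section gives the same blindfolded task, the same three directions and three repetitions per direction, and reports "good test-retest reliability (ICCs = 0.73-0.84").

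**Analysis.** Under Statistical analysis, "Differences in mean change (baseline minus follow-up) will be compared between groups using baseline values of the outcomes as covariates". The screening JPE has no role beyond eligibility.

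**The concern.** JPE is a primary outcome, and the article's own reliability figures show that a single reading carries appreciable measurement error. A single noisy covariate explains less of the follow-up variance than two readings of the same quantity. If the screening value exists for everyone enrolled, using it costs no extra measurement. It precedes randomisation, so adjusting for it cannot bias the comparison. What is at stake is the width of the intervals for the JPE contrasts, not the validity of the planned analysis.

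**Working it through.** **Inputs from the article**
- Test-retest ICC for JPE: 0.73-0.84 (Cervical JPE).
- Entry threshold: mean absolute error above 4.5° in any direction (Participants).
- 35 per group needed, 42 per group recruited, 20% dropout; JPE difference 4.5°, SD 3.2° (Sample size). Analysed number: 4 × 35 = 140 as planned for, or 168 × 0.8 = 134.4.

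**Assumptions not in the article**
- Screening and baseline readings are separate and equally reliable.
- The true (error-free) correlation ρ between baseline and follow-up is 0.3-0.9.
- For the entry-rule check only: population mean 4-6° and SD 2.0-3.2°.

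**Formula.** With baseline as a covariate, analysing change or the follow-up value gives the same residual variance. If follow-up has the same reliability, the observed correlation of one pre-treatment reading with follow-up is r = ICC × ρ. Then:
- residual variance, baseline only: 1 − r²
- residual variance, both readings: 1 − 2r²/(1 + ICC)
- ratio = [1 − 2r²/(1 + ICC)] / (1 − r²)

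**Results, ignoring the entry rule**

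| ICC | ρ | r | Both | Baseline only | Ratio |
|---|---|---|---|---|---|
| 0.73 | 0.3 | 0.219 | 0.9446 | 0.9520 | 0.992 |
| 0.84 | 0.3 | 0.252 | 0.9310 | 0.9365 | 0.994 |
| 0.73 | 0.6 | 0.438 | 0.7782 | 0.8082 | 0.963 |
| 0.84 | 0.6 | 0.504 | 0.7239 | 0.7460 | 0.970 |
| 0.73 | 0.9 | 0.657 | 0.5010 | 0.5684 | 0.881 |
| 0.84 | 0.9 | 0.756 | 0.3788 | 0.4285 | 0.884 |

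The ceiling is ρ = 1, where r equals the ICC. The ratios are then 0.822 and 0.792, a cut of 18-21%. That would require no true change in people's ranking through treatment and follow-up, so it is not used as the range.

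**Entry rule.** Selecting on screening JPE narrows the spread of that reading and trims the gain. A simulation with three directions and entry when any exceeds 4.5° at screening gave ratios of 0.887-0.982 for ρ of 0.6-0.9. At ρ = 0.3 the ratio stays just above 0.99, a gain slightly under 1%.

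**In practical terms**, taking ratios of 0.99 to 0.887:
- Interval width: √0.99 = 0.995 and √0.887 = 0.942, so about 0.5-6% narrower.
- Equivalent participants: 134.4 × (1/0.99 − 1) = 1.4 and 134.4 × (1/0.887 − 1) = 17.1. On 140 the figures are 1.4 and 17.8.

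**Interaction power at the stated figures.** The standard error of the interaction contrast is 3.2 × √(4/35) = 1.08°. For 4.5°, 4.5/1.08 − 1.96 = 2.20, so power is above 98%. For half that, 2.25/1.08 − 1.96 = 0.12, so power is about 55%.

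**The case against.** **The planned analysis is not wrong.** Comparing change with the baseline value as covariate is standard and unbiased. This stands: the point is about unused efficiency. It concerns a covariate choice that the article states, so it is not a complaint about detail left to an analysis plan.

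**Two readings are inferred.** The article gives no interval or separate visit between examination and baseline. It also says the examining physiotherapist will be blinded to allocation for those accepted, which would be odd for someone who acts only before randomisation. That suggests one person may both screen and assess later; it does not show that one reading serves both purposes. Eligibility testing is placed before enrolment and baseline assessment among those already eligible, so two readings is the more natural interpretation. A reader might take it as established, and the text does not go that far.

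**Equal reliability is assumed.** The ICC is quoted for the laser method at 90 cm. The screening description gives neither apparatus nor distance, and if the examiners differ there is no inter-rater figure. This stands: a less reliable screening reading would add less.

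**The size is uncertain and may be trivial.** The follow-up correlation is not given, and treatment in every arm plus a 12-month horizon could make it low. This also stands, and is why the range starts at about 1%.

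**Power is not the problem.** A reader might infer that the sensorimotor-by-balance interaction is weakly powered and needs rescuing. At the stated 4.5° and SD 3.2° it is not. Only smaller effects, such as half that difference, are at moderate power, and the article does not name them as targets.

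**Conclusion.** The point holds as a modest, optional gain in precision for JPE. On the more natural reading of the article, a pre-randomisation screening JPE exists for each enrolled participant and is left out of the adjustment. Using it would lower residual variance by roughly 1-11%. This rests on separate readings, equal reliability of 0.73-0.84 and a true baseline to follow-up correlation of about 0.3-0.9. The gain is an expected one, so an individual interval at the low end may not visibly narrow, and it probably shrinks towards 12 months.

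The documents do not support a claim of bias, contradiction or inadequate power for the stated difference. Nor does the point extend to postural sway: balance is screened with a timed tandem stand, not the sway meter.

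**What to change.** In Statistical analysis, for JPE only, add the screening JPE as a second covariate beside the baseline value: the same direction if directions are analysed separately, or the mean over directions if that is analysed. Keep the baseline assessment as the reference for change. The screening value was used to select people above 4.5°, so as a reference it would build in regression to the mean.

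State whether the screening and baseline readings are separate; if one reading serves both purposes, make no change. The cost is a line of wording and one model degree of freedom, with no new measurement. Fix it before the analysis so that the covariate is not chosen after seeing the results.
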